**Fig 1 pone.0267581.g001:**
[figure not shown]
MINGLE pilot trial schedule of enrolment, interventions, and assessments.

#### Phase 1

Participants for the semi-structured interviews will be recruited over three months or until data saturation is achieved. Interviews will be conducted in-person in a private room at the eye clinic or over the telephone depending on the participant’s preference and/or COVID-19 restrictions at the time. The inclusion criteria for Phase 1 are: 1) diagnosis of any form of AMD, 2) fluent English and 3) consent to participate in the study (including audio recording). Patient eligibility and interests will be screened by the researcher who will provide an explanation of the study. Informed verbal consent will be audio recorded and documented in a Record of Verbal Consent form.

#### Phase 2

Recruitment for Phase 2 will commence after the preliminary findings from Phase 1 have been identified. These findings will help to inform any modifications to the MINGLE program prior to conducting the pilot study. Participants will be recruited over six months or until the sample size target of 52 AMD patients is achieved. The inclusion criteria for Phase 2 are: 1) diagnosis of any form of AMD, 2) fluent English, 3) access to a smart phone, tablet or laptop with a front-facing camera; 4) technical ability to use Zoom or have someone to help; 4) clearance to safely participate in the physical activity components of the intervention (Physical Activity Readiness Questionnaire (PARQ+ [19]) or written physician clearance for participation) and; 5) written informed consent to participate. Specific exclusion criteria for Phase 2 are: 1) best-corrected visual acuity of worse than 6/60 (legal blindness) in both eyes [20]; 2) unable to ambulate/walk for exercise; 3) serious illness (including mental and cognitive illness) limiting their ability to exercise or complete the trial; 4) contraindications to exercise (i.e., failure to fulfil the prerequisites of the PARQ+); 5) uncontrolled hypertension (≥160/>90 mmHg); 6) signs or symptoms of alcohol/substance abuse and; 7) unable to commit to attending ≥80% of the sessions. Participation in Phase 1 of this study is not an exclusion criterion.

### Semi-structured interviews in Phase 1

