The Active Australia Survey is a 13-item, self-administered questionnaire to measure the frequency and duration of recreational physical activity in the last week as well as knowledge about the health benefits of physical activity [23]. The knowledge component of the survey is presented as a five-point Likert scale with response options ranging from ‘Strongly Disagree’ to ‘Strongly Agree’ [23]. This instrument can be implemented via computer-assisted telephone interviewing or in face-to-face interviews and is the recommended Australian population-based physical activity survey [23, 24].The Short Dietary Questionnaire for Age-related Macular Degeneration (SDQ-AMD) was used in the aforementioned telehealth intervention for people with AMD to capture dietary intake in the last week [25]. Response options to each food item is expressed as either serves consumed per day or per week, or number of times consumed per week [25]. The SDQ-AMD was adapted from a validated questionnaire [26] to capture intake of key food groups linked to AMD management. A question about dairy intake has also been added given evidence of a protective association between dairy intake and AMD [27]. The scoring criteria for the SDQ-AMD has been described previously [17] however will also be modified to provide a score for dairy intake.National Eye Institute Visual Function Questionnaire-25 (VFQ-25) is a reliable and valid instrument to capture vision function in people with AMD [28]. This instrument contains questions on the following sub-scales: general health; general vision; expectations; wellbeing/distress; ocular pain; near vision; distance vision; peripheral vision; social function; colour vision; driving; role limitations; and dependency [29]. The VFQ-25 scores are reported as an average of the items within each sub-scale [29].Falls Self-Efficacy Scale–International (FES-I) is a 16-item questionnaire to assess participants’ concerns about their possibility of falling [30]. Response options are presented on a four-point Likert Scale ranging from ‘Not at all concerned’ to ‘Very concerned’. Total scores range from 16 to 64 where a score of 16–19 indicates ‘low concern’; 20–27 is ‘moderate concern’; and 28–62 is ‘high concern’ [30].De Jong Gierveld Loneliness Scale is valid 6-item questionnaire to reliably capture overall, emotional and social loneliness [31]. This scale was similarly used in our WTL-Z RCT among older adults living in the United Kingdom. Scores range from 0 (not lonely) to 6 (extremely lonely). The guide suggests that the following items should be reversed before scoring: “There are plenty of people I feel close to”; “There are many people I can completely trust”; and “There are enough people I feel close to” [31].The Assessment of Quality of Life-8 Dimensions (AQoL-8D) is a 35-item questionnaire that includes eight individually scored dimensions [32]. The AQoL-8D comprises the 6 dimensions within the AQoL-6D (i.e., independent living; relationships; mental health (including depression); coping; pain; and senses) with two additional dimensions (i.e., self-worth; and happiness) [32]. The scoring guide for each dimension have been developed by the researchers at Monash University, Australia who developed the instrument (Assessment of Quality of Life, n.d.). In brief, the score ranges for each dimension are as follows: 4 to 22 (independent living); 7 to 34 (relationships); 8 to 41 (mental health); 3 to 15 (coping); 3 to 13 (pain); 3 to 16 (senses); 3 to 15 (self-worth); and 4 to 20 (happiness) [32].The ‘Attitude to Falls-Related Intervention Scale’ (AFRIS) [33] will be administered pre-post intervention to assess participant acceptability of the program. This will be achieved by comparing the pre-post mean total scores of participants offered the intervention, with possible scores ranging from 6 to 42 i.e., ‘less positive’ to ‘more positive’ attitude towards the intervention [33].

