
In addition to the AFRIS, the following approaches will be used to assess the acceptability and feasibility of the MINGLE program. 1) A 30-minute feedback discussion to reflect on the MINGLE program will be held immediately after the tenth session of the program. Participants will be invited to join the discussion by remaining online after completing their tenth session. Participants will be asked to reflect on a range of topics including their program experience; suggestions on how to improve the program; and the program’s potential for a large-scale roll-out. 2) A short feedback form will be included in the post-intervention questionnaire. This will include open- and close-ended questions covering level of satisfaction with the program, self-determined adherence to the program, and general feedback (e.g., suggestions to improve the program). 3) Attendance data will also be collected on all participants to allow for reporting on: the number sessions attended, completed sessions (‘dose’ of intervention received), and reasons for missed sessions. The session content will be tracked via checklists completed after each session allowing for reporting on the extent to which the intervention content is delivered per protocol and percentage of participants engaging/completing the activities.

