### Outcome measurement

Data collected on the abovementioned measures will be used to evaluate the program’s preliminary efficacy and its acceptability and feasibility. Specifically, this includes an evaluation of: 1) recruitment strategies–identifying the reach of each recruitment source; 2) recruitment rates at each stage of the project i.e., total number who expressed an interest in Phase 1 or 2, proportion who were eligible, provided consent, and completed the baseline questionnaire; 3) program adherence based on self-reported adherence and the Research Assistant’s evaluation during each session; 4) attrition rate; 5) pre-post responses to the AFRIS questionnaire; and 6) qualitative data obtained from the feedback survey and focus group discussion immediately post-intervention (Fig 1). The feedback survey includes Likert scales to rate overall satisfaction with the program and adherence to the nutritional advice provided, two Yes/No questions to determine whether participants would recommend the program to a friend and if the program was worthwhile, and two open-ended questions to identify the most useful or valuable components of the program, and for additional suggestions to improve the program.

Secondary outcome measures include participant-specific outcomes including a significant reduction in loneliness according to the De Jong Gierveld Scale, after completion of the 10-week MINGLE program, and significant changes in depression; quality of life; falls self-efficacy; physical activity (level) and overall diet using the AQoL-8D’s mental health dimension, overall AQoL-8D, FES-I, Active Australia Survey, and SDQ-AMD, respectively.

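### Acceptability is liable to be overstated: the feedback discussion reaches only session-10 completers, and no route is described for obtaining views at withdrawal

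*Protocol article*

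**What the plan says.** The protocol article's Introduction gives acceptability and feasibility in visually impaired older adults as the reason for the pilot. The Measures section provides four sources of evidence.

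- **AFRIS**, given before and after the program and evaluated by "comparing the pre-post mean total scores of participants offered the intervention".
- **A 30-minute group discussion** straight after the tenth session. "Participants will be invited to join the discussion by remaining online after completing their tenth session". Its topics include the potential for wider roll-out.
- **A feedback form** on satisfaction and self-rated adherence. "A short feedback form will be included in the post-intervention questionnaire". Outcome measurement adds items on whether the participant would recommend the program and found it worthwhile.
- **Attendance.** "Attendance data will also be collected on all participants to allow for reporting on" sessions attended, sessions completed and reasons for missed sessions.

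Outcome measurement also lists the attrition rate and "program adherence based on self-reported adherence and the Research Assistant’s evaluation during each session".

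According to Measures, the post-intervention questionnaire goes to all Phase 2 participants immediately after the 10 weeks. Under Data collection and analysis plan (Phase 2), staff prompt its return and missing values are filled by carrying the last observation forward. The Phase 2 exclusion criteria under Recruitment include being "unable to commit to attending ≥80% of the sessions".

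**The concern.** People who leave a program early are the ones most likely to have found it unsuitable. A group discussion that starts when session 10 ends cannot include anyone who is absent by then. The form can reach someone who left in an early week, but only weeks later and inside a long online questionnaire. The protocol describes no attempt to ask for views when a person withdraws.

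The missing-data rule does not close the gap. A withdrawer's AFRIS would be filled with the pre-program value, that is, with no change in attitude. The satisfaction, recommendation and worthwhile items are asked only once, so there is no earlier value to carry forward and a proportion would by default be taken over responders.

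At stake is the reading of the pilot. A high satisfaction percentage could reflect who was left to answer as well as the program itself, and it would be carried into the planning of a larger study.

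**Working it through.** **The plan's own figure.** The Phase 2 target of 52 is used here only as the denominator. It reproduces: a paired t-test with d = 0.4 and 80% power needs n = 52 (power 0.808) at two-sided alpha 0.05. The article does not state alpha or sidedness, so these are assumed. The point does not dispute this number.

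**Inputs for the bounds.**
- N = 52 (Sample size considerations, Phase 2).
- Response rate r: 88%, 80% or 70%. The first is the retention of the earlier hearing-loss trial cited in the same section, used here as if it were a response rate. The other two are assumptions.
- Acceptability among responders: about 95%. This is an assumption, suggested by the at least 95% reported for that earlier trial.
- Acceptability among non-responders: unknown, so taken from 0% to 100%.

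**Formulas.** Let m = N × r, rounded, be the responders and a = 0.95 × m, rounded, those who find the program acceptable.
- Responder figure = a/m
- Lowest whole-group figure = a/N
- Highest whole-group figure = (a + N − m)/N
- Half of non-responders favourable = (a + 0.5(N − m))/N
- Maximum overstatement = a/m − a/N

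| Response | Responder figure | Lowest over 52 | Half favourable | Highest over 52 | Maximum overstatement |
|---|---|---|---|---|---|
| 88% (m = 46) | 44/46 = 95.7% | 44/52 = 84.6% | 47/52 = 90.4% | 50/52 = 96.2% | 11.0 points |
| 80% (m = 42) | 40/42 = 95.2% | 40/52 = 76.9% | 45/52 = 86.5% | 50/52 = 96.2% | 18.3 points |
| 70% (m = 36) | 34/36 = 94.4% | 34/52 = 65.4% | 42/52 = 80.8% | 50/52 = 96.2% | 29.1 points |

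The highest figure is slightly above the responder figure in every row. The bias is therefore not certain in direction, but it has far more room downwards than upwards.

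**AFRIS under the carry-forward rule.** The true mean change over all enrolled is r × (change in responders) + (1 − r) × (change in non-responders). Carrying forward sets the second term to zero. With 6 of 52 missing, each point by which non-responders' mean score has really fallen makes the reported mean too favourable by 6/52 = 0.12 points. If their attitude had improved, the error would run the other way.

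**Adherence.** Attendance, dose received and reasons for missed sessions cover everyone enrolled, so dropout lowers these figures as it should. Only the self-rated part depends on returning the form. With 10 sessions, the entry commitment corresponds to 8 sessions, so the attendance result describes people already screened on that intention.

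**The case against.** The strongest reply is that the plan does ask everyone. The questionnaire containing the form goes to all Phase 2 participants, with staff prompts, and nothing limits it to people still attending. AFRIS is defined on those offered the intervention. Non-response affects any questionnaire, and a condensed article may leave follow-up of withdrawers to the full protocol. All of this stands, and it rules out saying that withdrawers are never asked. What remains is what the article itself fixes: when and how the discussion is offered, the single week-10 placement of the form, and a missing-data rule that cannot recover later views.

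A reader might infer more than the text supports:
- **That acceptability will certainly be overstated.** Response rates and non-responders' views are unknown, and the bounds include a small error in the opposite direction.
- **That adherence is also overstated.** Attendance and attrition cover all enrolled. The 80% commitment is openly stated. It limits whom the result applies to and does not bias it within the enrolled group.
- **That recruitment rates are distorted** because the funnel begins with "total number who expressed an interest in Phase 1 or 2, proportion who were eligible, provided consent, and completed the baseline questionnaire". Flyer respondents approach the researcher themselves, and telephone contacts have already shown interest in research, so this is a natural start. The reach of each recruitment source is also to be reported. A different start is a reporting preference.
- **That Phase 1 interviewees will inflate the ratings,** since "Participation in Phase 1 of this study is not an exclusion criterion". The overlap is unknown, and that they would go unidentified in the analysis is inferred from silence.

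The article also sets no acceptability threshold or roll-out rule, so the harm lies in interpretation and no stated decision is shown to be wrong.

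**Conclusion.** The point holds in a limited form. Evidence on acceptability comes mainly from people who complete the program or return the week-10 questionnaire, no route for views at withdrawal is described, and the carry-forward rule would hide a worsened AFRIS. The likely direction is upward, because withdrawers are plausibly less satisfied, but this is not proven. The maxima of about 11 points at 88% response and 18 points at 80% are worst cases. They assume about 95% acceptability among responders and none among non-responders. If half of the non-responders were favourable, the gaps would be 95.7 − 90.4 = 5.3 points and 95.2 − 86.5 = 8.7 points. For adherence the conclusion concerns scope only: it applies to people who committed in advance to the attendance level. The sample size is not affected. This is an inexpensive improvement to a central pilot outcome, not a fault that undermines the study.

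**What to change.** 1. Send the existing short feedback form to each participant at withdrawal or at week 10, whichever comes first.
2. Invite all enrolled participants to the feedback discussion, including those absent from session 10.
3. Report acceptability with all enrolled as the denominator beside the responder figure. Add a sensitivity analysis that counts missing answers as not acceptable, and do not rely on carried-forward AFRIS scores for withdrawers.
4. Beside the adherence result, give the number of people excluded solely because they could not make the 80% attendance commitment.

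The cost is a few extra e-mails or calls and a count from the screening records. The intervention and the sample size stay as they are. The acceptability figure may look less favourable.

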### Outcome measurement

Data collected on the abovementioned measures will be used to evaluate the program’s preliminary efficacy and its acceptability and feasibility. Specifically, this includes an evaluation of: 1) recruitment strategies–identifying the reach of each recruitment source; 2) recruitment rates at each stage of the project i.e., total number who expressed an interest in Phase 1 or 2, proportion who were eligible, provided consent, and completed the baseline questionnaire; 3) program adherence based on self-reported adherence and the Research Assistant’s evaluation during each session; 4) attrition rate; 5) pre-post responses to the AFRIS questionnaire; and 6) qualitative data obtained from the feedback survey and focus group discussion immediately post-intervention (Fig 1). The feedback survey includes Likert scales to rate overall satisfaction with the program and adherence to the nutritional advice provided, two Yes/No questions to determine whether participants would recommend the program to a friend and if the program was worthwhile, and two open-ended questions to identify the most useful or valuable components of the program, and for additional suggestions to improve the program.

Secondary outcome measures include participant-specific outcomes including a significant reduction in loneliness according to the De Jong Gierveld Scale, after completion of the 10-week MINGLE program, and significant changes in depression; quality of life; falls self-efficacy; physical activity (level) and overall diet using the AQoL-8D’s mental health dimension, overall AQoL-8D, FES-I, Active Australia Survey, and SDQ-AMD, respectively.

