### Sample size considerations

#### Phase 1

Participants for Phase 1 will be recruited until data saturation is achieved, that is, when the interviews no longer provide new information or knowledge to the researchers about an AMD patient’s perspective on participating in the MINGLE program. According to our previous research investigating the barriers and facilitators to participating in a mental wellbeing program among people with AMD [34], approximately 30 participants were required to achieve this.

#### Phase 2

A minimum of 52 participants are required to achieve a pre-post change in the primary outcome (i.e., loneliness), assuming a 0.4 effect size according to Cohen’s d and 80% power (G*Power 3.1 software). An effect size of 0.4 was chosen as the average effect size of our previous WTL-related work i.e., 0.43 [35] and 0.35 [16] for loneliness using the De Jong Gierveld Scale. The later study also proved to be feasible and acceptable demonstrating ≥ 80% adherence rate, 88% retention rate and was acceptable or highly acceptable by ≥ 95% of participants [16].

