### Data collection and analysis plan

#### Phase 1

Semi-structured interviews will be conducted Data for all participants will be audio recorded and transcribed verbatim using an external transcribing service. Transcripts will be analysed iteratively to ensure analytic reflexivity. Two members of the research team with a vision science and/or ophthalmology background will deductively code the transcripts using content analysis [36] based on the Capability, Opportunity, Motivation and Behaviour (COM-B) model of the behaviour change wheel [37]. Codes will be discussed, and consensus reached with other members of the research team. Themes will be established under each subset of the COM-B model relating to barriers and facilitators to participating in an interactive online program. Phase 1 findings will inform the design of MINGLE.

#### Phase 2

Data for all participants will be collected via online self-report pre-post questionnaires administered via REDCap. Participants will be prompted to complete and return questionnaires by study staff to promote participant retention. All data will be entered into REDCap. Only staff directly involved in the study will have access to the databases. Statistical analysis will be carried out using IBM SPSS Statistics V.25. Descriptive statistics will be used to assess the acceptability and feasibility of MINGLE and the pre-post intervention changes in loneliness, depression, falls self-efficacy, physical activity, and dietary intakes. For missing data, the last observations will be carried forward prior to data analysis.

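### Six participant-level outcomes are worded as reaching significance, although only loneliness is sized and the analysis section plans descriptive statistics; the five unsized outcomes should be worded as exploratory

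*Protocol article*

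**What the plan says.** Three sections of the protocol article bear on this.

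- **Outcome measurement.** The paragraph opens with "Secondary outcome measures include participant-specific outcomes". It then names "a significant reduction in loneliness according to the De Jong Gierveld Scale, after completion of the 10-week MINGLE program" and, in the same sentence, "significant changes in depression; quality of life; falls self-efficacy; physical activity (level) and overall diet using the AQoL-8D’s mental health dimension", followed by the remaining instruments. That makes six outcomes: loneliness, depression, overall quality of life, falls self-efficacy, physical activity and diet. Significance is part of how each is worded. No significance level is given.
- **Sample size considerations, Phase 2.** "A minimum of 52 participants are required to achieve a pre-post change in the primary outcome (i.e., loneliness), assuming a 0.4 effect size". Loneliness is the only outcome sized, and here it is primary.
- **Data collection and analysis plan, Phase 2.** "Descriptive statistics will be used to assess the acceptability and feasibility of MINGLE and the pre-post intervention changes in loneliness, depression, falls self-efficacy", with physical activity and dietary intakes completing the list. Overall quality of life is not on it. No hypothesis test is named.

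The Abstract and Introduction describe Phase 2 as a non-randomised pilot of feasibility, acceptability and preliminary efficacy.

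**The concern.** The outcome section sets a bar, significance, that the analysis section has no means of applying, since descriptive statistics cannot show that a change is significant. Whoever writes the results must follow one section or the other. Someone who follows the outcome section will run six tests, five of them on outcomes the study was not sized for, and may report whichever fall below 0.05.

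The study has no control group, so there is no comparison against which a chance shift, or a shift due to time alone, would be recognised. One or two isolated small p-values could then be read as signs that the program works, and could be carried into the planning of a larger trial. The article itself sizes this study on effect estimates from related earlier work, one of them from a pilot trial.

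**Working it through.** **Inputs**

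| Input | Value | Source |
|---|---|---|
| Outcomes worded by significance | 6 | Outcome measurement |
| Sample size | 52 | Sample size considerations, Phase 2 |
| Effect size and power | d = 0.4, 80% | Same section: "assuming a 0.4 effect size according to Cohen’s d and 80% power" |
| Significance level and sidedness | Not stated | Inferred in step 1 |
| Correlation between outcomes | Not stated | Varied from 0 to 0.9 |

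**Step 1. Reproduce the 52.** For a paired t-test the noncentrality is d√n = 0.4 × √52 = 2.88 on 51 degrees of freedom. At two-sided 5% the power is 80.8%, and 52 is the smallest n that reaches 80%. At one-sided 5% and the same d, 41 would be enough; at two-sided 1%, 77 would be needed. The stated effect size and power therefore point to a two-sided 5% test. This is an inference, because the article does not state the level.

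**Step 2. Six independent outcomes with no true change, each tested at 5%.**

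1 − (1 − 0.05)^6 = 1 − 0.7351 = 0.265, or 26.5%.

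The expected number of false significant results is 6 × 0.05 = 0.3, whatever the correlation.

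**Step 3. Correlated outcomes.** One million draws of six equally correlated normal test statistics, each compared with the two-sided 5% limit:

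| Common correlation | Chance of at least one false significant result |
|---|---|
| 0.1 | 26.2% |
| 0.3 | 24.1% |
| 0.5 | 20.7% |
| 0.7 | 16.4% |
| 0.8 | 13.8% |
| 0.9 | 10.8% |

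A separate simulation with actual paired t-tests on 52 pairs gave 26.6%, 21.0% and 13.9% at correlations 0, 0.5 and 0.8, so the normal approximation is adequate.

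**Step 4. Two sensitivity checks.**

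- The depression measure is one dimension of the AQoL-8D, so it must overlap with the overall score. Setting that pair at 0.8 (assumed) and all other pairs at 0, 0.3 or 0.5 gives 25.0%, 23.0% and 20.1%.
- With all six tests one-sided at 5%, the figures are 26.5% at correlation 0, 18.6% at 0.5 and 10.0% at 0.9. Sidedness matters little.

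**Step 5. The five unsized outcomes alone.** 1 − 0.95^5 = 22.6% if independent; by simulation, 18.3% at correlation 0.5 and 10.2% at 0.9. Most of the excess comes from these five.

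**Step 6. Splitting the level instead.** 0.05/6 = 0.0083 per test brings the overall rate to 1 − (1 − 0.0083)^6 = 4.9% under independence, but power for loneliness at d = 0.4 with 52 pairs falls from 80.8% to 55.9%.

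**The case against.** The strongest reply is that the analysis section governs, and it plans no tests. On that reading there is no error rate to inflate, and the percentages above belong to an analysis nobody has specified. Much of this stands: the figures are conditional on the outcome section being applied as worded. It does not remove the point, for three reasons. The outcome section still asks for significance. A sample size based on "80% power (G*Power 3.1 software") presupposes a test, at least for loneliness. And for overall quality of life the outcome section's wording is the only criterion given.

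A second reply is that multiplicity handling is usually left to an analysis plan, which is not shown here, and that unadjusted secondary outcomes are conventional in a pilot. That is right. A reader might infer that the missing alpha split or testing order is itself a fault; the documents do not support this. The point concerns the significance wording that the article does contain.

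A third stronger reading is that there is no hierarchy at all. That goes too far, because the sample size section names loneliness as primary. The hierarchy is contradictory rather than absent.

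Finally, no rule says that one positive outcome out of six is enough. True, but nothing in the article discourages that reading either, and the conflict between sections leaves it open.

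**Conclusion.** The point holds as a conflict of wording with a measurable consequence. Six outcomes are worded by significance, one is sized, and the planned analysis is descriptive. If the outcome section is applied with each test at two-sided 5%, the chance of at least one false significant result when nothing has changed lies between about 11% (correlation 0.9) and 27% (independence), and is about 21% at correlation 0.5. Across that range it is at least twice the level of a single test.

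This rests on two assumptions that the article does not state: the 5% level, inferred from n = 52, and the correlation. No single percentage should be quoted as the study's error rate, and the article does not claim to hold a 5% rate across outcomes. For a pilot of preliminary efficacy this is a cheap improvement and does not undermine the design.

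**What to change.** - **Outcome measurement:** remove the significance wording for depression, quality of life, falls self-efficacy, physical activity and diet. State that these five are exploratory, reported as mean pre-post change with an unadjusted 95% confidence interval, without any claim of significance or efficacy.
- **Data collection and analysis plan, Phase 2:** add overall quality of life to the list of changes described, so that the two sections cover the same six outcomes.
- **Loneliness:** keep at most one significance test, on the pre-post change in the De Jong Gierveld score, and state its level and sidedness. Two-sided 5% is what the 52 participants imply, and power then stays at 80.8% for d = 0.4 with 52 complete pairs.
- **Status of loneliness:** make the outcome and sample size sections agree on whether it is primary or secondary.

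The cost is wording only, with no extra participants or data. What is given up is the option of reporting an isolated p<0.05 on one of the five as a positive finding. A fixed testing sequence or a Holm adjustment after loneliness is optional if formal claims on the five are wanted; a pilot does not need it. Bonferroni across all six would cost too much power on the one outcome that was sized.
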